### Procedures

#### Pregnancy Surveillance and Birth Notification

Pregnancy surveillance was instituted as a continuous activity in the trial to identify and track new and existing pregnancies. A team comprising of 2 female community health workers per union councils is responsible for surveillance and birth notifications. Identified pregnancies in the intervention clusters are counseled on the KMC intervention and its benefits to mother and baby. At the same time, counseling on essential newborn care is given in the control areas.

The team also records pregnancy outcomes (ie, miscarriage, stillbirths, and live births), and all registered live births are followed up for mortality outcomes at 28 days of life. Other additional sources for birth notifications are the female health workers, village elders, and traditional birth attendants, who support the study teams and provide regular reports on births in their respective areas.

#### Screening, Recruitment, and Intervention Delivery

When a birth is reported, the recruitment and intervention teams will visit the household within 72 hours of the delivery. The screening and recruitment are carried out by a separate team, comprising of a male team leader and 2 community health workers. Once the eligibility criteria are fulfilled and consent from the mother or caregiver is recorded, the mother-baby dyad is recruited in the study. After recruitment, the team visits the household on days 5, 7, 10, 14, 21, and 28 in the intervention clusters to support KMC practice. They will demonstrate the steps of KMC, including KMC positioning with the support of a “chaddar” (a cloth that females use to cover their heads and body for modesty) and IEC material. The LBW babies in the control clusters will receive standard essential neonatal care as per the national guidelines. The intervention team also conducts 1-on-1 and community-based mobilization for KMC advocacy.

#### Data Collection

Independent data collection teams comprising of 2 community health workers in each cluster will be deployed in both intervention and control clusters. The teams collect data on KMC compliance, anthropometry (weight and length), signs of PBSI, breastfeeding practices, and mortality on scheduled follow-ups at days 7, 28, and 59. On days 120 and 365, information on mortality, breastfeeding practices, infant and young child feeding practices, and nutrition status (weight and length) will be captured. In addition, a neurodevelopmental assessment will be performed on a subset of children using the Bayley’s scale at 12 months [32].

The data collection teams examine the baby for any symptoms of disease during each household visit. If symptoms of disease are observed, a prompt referral will be made to the nearest health facility. Participant mothers willing to comply but unable to perform KMC for 1 week or more due to illness or other reasons are excluded from the study. Loss to follow-up is defined as the unavailability of a mother-baby dyad for 3 consecutive follow-ups after recruitment.

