**Methods:**

We designed a community-based cluster randomized controlled trial in one rural district of Pakistan. Stable, LBW babies (weighing 1200 grams to 2500 grams) are included in the study. The community KMC package, consisting of the KMC kit, information and counseling material, and community mobilization through KMC champions (village volunteers), was designed after preliminary research in the same geographical location and implemented in intervention clusters. The standard essential newborn care is offered in the control clusters. Infants are recruited and followed up by independent teams of data collectors. Data are collected on the duration of skin-to-skin contact, growth, breastfeeding practices, morbidities, neonatal mortality, and neurodevelopment status. Data analysis will be conducted based on the intention to treat principle. The Cox regression model will be used to assess the primary outcome of neonatal mortality. The secondary outcomes will be evaluated using linear or logistic regression.

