### Data Analysis

For data analysis, we will use the intention to treat approach using STATA software (version 17; StataCorp). Data will first be analyzed using person-time as the denominator for the primary outcome (neonatal mortality between enrollment and 28 days of age). Hazard ratios and 95% CIs will then be calculated using a Cox regression model to evaluate the effect of the intervention (cKMC) on infant deaths. We will also estimate the impact of cKMC using the number of enrolled infants as the denominator to deduce risk ratios using generalized linear models of the binomial family with a log link function. The summary data for background characteristics in the intervention and control groups will be presented as means and proportions.

The effect of KMC on secondary outcomes (ie, exclusive breastfeeding, weight and length gain, the incidence of illnesses and hospitalizations, and care-seeking behavior) will be assessed using linear or logistic regression after adjusting for clustering in the case of twins or another enrolled baby subsequently born to the same mother, as well as other potential confounders.

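### Enrolled mothers who are willing but unable to practise KMC for a week or more are excluded from the study, which conflicts with the stated intention-to-treat analysis and can bias the mortality comparison

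*Protocol article*

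**What the plan says.** The Data Collection section of the protocol article, next to the definition of loss to follow-up, states of participating mothers who are ready to practise KMC that those "unable to perform KMC for 1 week or more due to illness or other reasons are excluded from the study".

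The analysis commitments point the other way. The abstract's Methods paragraph says "Data analysis will be conducted based on the intention to treat principle". The Data Analysis section says "For data analysis, we will use the intention to treat approach using STATA software". It defines the primary outcome as "neonatal mortality between enrollment and 28 days of age" and describes the risk-ratio analysis as "using the number of enrolled infants as the denominator to deduce risk ratios".

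On timing, Screening, Recruitment, and Intervention Delivery says that "the recruitment and intervention teams will visit the household within 72 hours of the delivery". The same section limits household visits in support of KMC to the intervention clusters and gives control infants standard essential care. Pregnancy Surveillance and Birth Notification, and Training of Study Teams, draw the same line between arms for antenatal counselling and for health-worker orientation. The surveillance team is also said to establish day-28 mortality for every live birth on its register.

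**The concern.** An intention-to-treat analysis keeps each enrolled infant in the arm of its cluster whatever happens afterwards. The exclusion depends on something that happens after enrolment and is part of adherence to the intervention. One of its two stated grounds is illness, which plausibly goes with the risk of death before day 28. The other ground is left open, in a trial that cannot be blinded.

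If infants leave one arm for such reasons and there is no like removal in the other, randomisation no longer protects the primary comparison. What is at stake is a distorted mortality ratio in either direction. The sentence also governs conduct: if follow-up stops when a dyad is excluded, a later analysis plan can analyse only what was still collected.

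**Working it through.** **1. Is it an eligibility rule?** No. Eligibility is set out under Inclusion and Exclusion Criteria, and this rule is not there. Screening and recruitment fall within 72 hours of delivery, so a week of inability must run past that window. The sentence also speaks of mothers who are already participants.

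**2. Can all the statements hold together?** Not as worded. If an enrolled dyad leaves the study, its infant is either missing from the denominator, which contradicts the enrolled-infant denominator, or counted in it without complete follow-up to day 28. No section says that excluded dyads remain in follow-up or analysis.

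**3. Which arm does it act on?** The sentence names none, and data teams work in both arms. But being willing to comply presupposes having been asked to practise KMC, and control mothers are not asked. Applied literally to controls, the rule could remove much of that arm, which is not a credible intention. Operation almost only in the intervention arm is therefore an inference, though a strong one.

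**4. The plan's own figures.** From Sample Size: 25,000 × 29/1000 × 27.7% = 200.8 LBW births per cluster (stated as 200); 24 × 200 = 4800, or 2400 per arm. Control mortality is 13.3%; a 30% reduction gives 13.3% × 0.70 = 9.31%, a target risk ratio of 0.70.

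**5. Size of the possible bias.** Let x be the share of the intervention arm excluded and r the mortality of excluded infants relative to that arm's average. The protocol gives neither, so both are assumptions. With no true effect and excluded infants dropped entirely from the intervention arm only:

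apparent RR = (1 − x·r) / (1 − x)

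With 2400 infants at 13.3%, the arm has 319.2 expected deaths.

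| x | r | Excluded: infants, deaths | Retained: deaths / infants | Apparent RR |
|---|---|---|---|---|
| 5% | 2 | 120, 31.9 | 287.3 / 2280 = 12.6% | 0.90/0.95 = 0.95 |
| 10% | 2 | 240, 63.8 | 255.4 / 2160 = 11.8% | 0.80/0.90 = 0.89 |
| 10% | 0.5 | 240, 16.0 | 303.2 / 2160 = 14.0% | 0.95/0.90 = 1.06 |

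If r is instead defined relative to retained infants, the formula is 1/(1 − x + x·r), and the same three rows give 1/1.05 = 0.95, 1/1.10 = 0.91 and 1/0.95 = 1.05. The definition changes the second decimal, not the conclusion.

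If the true ratio were 0.70, the factors in the table would turn it into 0.70 × 0.947 = 0.66, 0.70 × 0.889 = 0.62 and 0.70 × 1.056 = 0.74.

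**6. Precision.** The smaller numbers matter little. If the design has exactly 90% power, excluding 5% or 10% of one arm lowers it to 89.2% or 88.3%. The problem is bias.

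**The case against.** The best defence is that the sentence may mean only withdrawal from further study procedures. The Data Analysis section names enrolled, not retained, infants as the denominator and counts deaths from enrolment. Data Management provides for a participant flow with reasons for exclusion recorded. The article also condenses a fuller protocol. That reading is possible, so the text does not prove that infants will be dropped from the analysis. But the article nowhere states it, and exclusion from the study is the natural meaning of the words, so the conflict stands.

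Several stronger inferences are tempting, and the documents do not support them:

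- **That the trial would compare adherent intervention dyads with all controls.** The rule covers only mothers who are willing but unable. Those who decline or neglect KMC are not covered and stay in.
- **That the protocol excludes from the intervention arm only.** It does not say so; this follows from where KMC is promoted.
- **That sick infants are removed.** The text does not say whose illness is meant, and the other reasons need not concern health.
- **That the bias must favour cKMC.** Illness pushes that way. But a dyad must usually get through a week before it can be excluded, so the infant has usually survived that period, which can push the other way.
- **That the distortion is very large.** With x = 10% and r = 3 the formula gives 0.70/0.90 = 0.78, but r = 3 means 3 × 13.3% = 39.9% of excluded infants dying by day 28. That is hard to reach when most must first survive the qualifying week.
- **That the damage cannot be undone.** For day-28 death it probably can, through birth surveillance.

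**Conclusion.** The point holds as a conflict within the protocol that touches the primary endpoint. The exclusion cannot be applied as written alongside an intention-to-treat analysis of all enrolled infants, and the passages must be reconciled.

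The size of any bias is unknown. Under the assumed inputs, and with no true effect, apparent ratios run from 0.89 to 1.06. At 0.89 the spurious reduction is 11%, about 11/30 = 37% of the 30% reduction the trial is designed to detect. This rests on three assumptions: that the rule acts almost only in intervention clusters, that excluded infants leave the analysis, and that their mortality differs from the arm average. If their mortality equals that average (r = 1), the ratio is not distorted. Inability first arising after day 28 does not affect the primary outcome, provided data already collected are kept.

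**What to change.** Delete the exclusion sentence. If it was meant only to end KMC support for these mothers, reword it to say that, with no effect on follow-up or analysis. Whether such support should continue is a clinical matter on which this point takes no position. Then:

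- State that every enrolled infant stays in scheduled follow-up and in the primary analysis, in the arm of its union council, whatever KMC was practised.
- Record inability to perform KMC, with its reason and dates, as an adherence variable. Use it only in a secondary analysis labelled as per-protocol or dose.
- For dyads already excluded, recover day-28 vital status from the surveillance of registered live births, return those infants to the primary analysis, and report the number excluded by arm with reasons.

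The text change is small. Data collection began in August 2019, so the rule may already have been applied. The article describes no linkage between surveillance and trial records, so some linkage work is likely. Surveillance as described stops at day 28, so missed visit-based outcomes such as weight, PSBI and breastfeeding may not be recoverable. These should be handled and reported as missing data.

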#### KMC Intervention Package

A cKMC package is developed to support mothers and overcome sociocultural barriers to practicing KMC. The package includes the following:

##### KMC Kit

The kit contains 20 diapers for the child, 10 napkins for the mother, 1 towel, a pair of socks and cap for the infant, 1 bar of soap, and an educational brochure in the local language. These items are packaged in a ziplock plastic bag. The recruitment team is responsible for providing the kit to enrolled mothers. 

##### Education Package

We have developed a contextual IEC package for parents and families to create awareness and describe the benefits of KMC for the survival and well-being of LBW newborns. The material comprises flip charts, wall mounts, and a self-explanatory video on the steps of KMC, its benefits, and the potential implementation of a buddy system (ie, skin-to-skin contact provided by other family members).

##### Community Mobilization (KMC Champions)

A community mobilization team (1 male and 1 female) conducts one-on-one and group sessions concerning essential newborn care and KMC practices with newly pregnant women, mothers, and mothers-in-law. The sessions are conducted at regular intervals. The male mobilizer is responsible for the one-on-one and group sessions advocating KMC with fathers and other male members of the community.

The community mobilization team also encourages the recruitment of volunteers to function as KMC champions. The local community members serving as KMC champions serve as catalysts for mobilization. The mobilization staff also identifies and recruits cochampions (other community volunteers) to be mentored by KMC champions. This group of local community members serve to disseminate KMC practices and facilitate uptake in the community.

A simple color-coded KMC calendar depicting 24 hours was designed in the local language for families of enrolled newborns to record the number of hours that the mother or buddy practices KMC. The mother and family members are instructed on how to use the calendar and asked to mark the number of hours KMC is practiced each day on the calendar. These data are collected at the end of each week.

### Outcome Ascertainment

The data are collected in a structured electronic format to ascertain outcomes. The anthropometric measurements are done per standard anthropometry guidelines [33] by the pair of measurers (weight and length). Infant weight is measured on pan scales (model 354; Seca) and length is measured by the infantometer (model 417; Seca). The details of the outcome measures are described in Textbox 1.

Outcome measures and definitions. LBW: low birthweight; PSBI: possible serious bacterial infection; EBF: exclusive breastfeeding defined as the percentage of infants aged 0 to 6 months who are exclusively breastfed; KMC: kangaroo mother care.**Reduction in neonatal mortality:** the reduction of mortality in LBW newborns during the first 28 days of life.**Improvement in growth (nutrition status):** the increase in newborn weight gain from birth and at days 14, 28, 59, 120, 180, and 365; and the increase in the length of the newborn from birth and at days 180 and 365.**Reduction in PSBI incidence:** the reduction in PSBI incidence during the neonatal period (days 14 and 28) and 59 days of life.**Improved EBF:** increase in the EBF rate up to 50% at 6 months of age.**Improved neurodevelopment:** KMC improves neurodevelopment outcomes while impairments in physical growth and brain and central nervous system development can result in cognitive, language, motor, neurosensory impairments, and behavioral disorders. Hence assessment will be done at 12 months of age.

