### Study Site

The study is being conducted in 2 subdistricts (Taluka-Johi and Taluka-Khairpur Nathan Shah) of the district Dadu, which is a rural agrarian district in Sindh province of Pakistan. The overall population of the 2 talukas is about 2 million people residing in 54 union councils. The union council is the smallest administrative unit in Pakistan, with 15,000 to 25,000 people. The study area's population is largely poor, with 68% of households belonging to the lowest wealth quintiles. The study area also has an LBW prevalence of 27.7%, with an exclusive breastfeeding rate of 17.3%. Half of the women still deliver at home, and the proportion of facility births is 48.8% [30].

The public sector primarily provides the health care in the target area. There are 2 secondary care hospitals in the study area. There is a basic health unit (BHU) in each union council, and 15 to 20 lady health workers (LHW) are affiliated with each BHU, serving as frontline health care providers for a population of 1000 people in their respective areas.

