### Study Population

#### Inclusion and Exclusion Criteria

All stable LBW newborns weighing 1200 grams to 2500 grams are screened within a 72-hour window, followed by enrollment after informed consent to participate in the trial is obtained. Newborns tolerating oral feeding with no respiratory distress, the absence of any symptoms of disease, and the absence of congenital anomalies are included in the study.

Whereas newborns weighing less than 1200 grams and with symptoms of disease according to predefined criteria (ie, unable to tolerate oral feeding; severe respiratory distress, including respiratory rates of less than 20 breaths per minute or more than 60 breaths per minute; grunting–central cyanosis; severe chest in-drawing; convulsions; unconsciousness; severe hypothermia of less than 32°C; apnea; and congenital malformation) are excluded and referred to the nearest health facility for management.

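### Weight and length gain are counted from birth, but the first trial contact described falls anywhere within 72 hours of delivery; the baseline should be the enrollment measurement, with baseline size and age at weighing in the model

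*Protocol article*

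**What the plan says.** - **Outcome.** Outcome Ascertainment (Textbox 1) defines weight growth as "the increase in newborn weight gain from birth and at days 14, 28, 59, 120, 180, and 365" and length growth as "the increase in the length of the newborn from birth and at days 180 and 365". Both start at birth.
- **First contact.** Under Inclusion and Exclusion Criteria, "All stable LBW newborns weighing 1200 grams to 2500 grams are screened within a 72-hour window". Under Screening, Recruitment, and Intervention Delivery, the teams "will visit the household within 72 hours of the delivery". No weighing at delivery is described.
- **Place of birth.** Study Site states: "Half of the women still deliver at home". It puts facility births at 48.8%.
- **Analysis.** Data Analysis lists "exclusive breastfeeding, weight and length gain, the incidence of illnesses and hospitalizations" among the secondary outcomes and assigns them linear or logistic regression. The adjustment it names is for clustering of infants of the same mother; further confounders are mentioned but not listed. Baseline size and age at weighing are neither included nor ruled out.
- **Masking.** The Randomization section says blinding is impossible and relies on a data collection team separate from the implementation team.

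**The concern.** The outcome needs a value at birth that the described procedures do not supply for many infants. For a home birth, the natural stand-in is the weight taken at screening to check the 1200 to 2500 g limits. That weight may belong to an infant a few hours old or three days old, a period in which newborn weight usually changes. Gain from that value mixes growth with age at first weighing.

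If visit timing is the same in both arms, the cost is added variability. If one arm is reached later, and infants are losing weight at that age, that arm starts from a lower baseline and appears to gain more at every later visit. The trial is unblinded and its community activities differ by arm, so equal timing should be shown, not assumed.

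The second issue is precision. A change score analyzed without baseline size as a covariate is never more precise than the baseline-adjusted analysis, and it can be much less precise.

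**Working it through.** The article gives no standard deviation, correlation, sample size or early weight-loss figure for growth, so there is no stated figure to reproduce. The inputs marked as assumed below are not in the document.

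**1. Time points side by side.** The definition requires birth (0 hours). Screening supplies one point between 0 and 72 hours. Facility records could supply a true birth weight for at most 48.8% of births, if they are used, which the article does not say. Using them for some infants and screening weights for the rest would mix two kinds of baseline.

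**2. Effect for one infant.** Assume that a fraction f of weight w is lost evenly over 72 hours. The baseline shift at h hours is w × f × h/72.
- For w = 2200 g (assumed) and f = 4 to 8% (assumed), the shift at 72 hours is 2200 × 0.04 = 88 g to 2200 × 0.08 = 176 g.
- A wider assumption of 3 to 10% across the eligible range gives 1200 × 0.03 = 36 g to 2500 × 0.10 = 250 g.

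**3. Effect on the arm comparison.** Only a difference in mean age at first weighing matters here.
- 12 hours at 4%: 2200 × 0.04 × 12/72 = 14.7 g.
- 24 hours at 8%: 2200 × 0.08 × 24/72 = 58.7 g.
- No difference in timing: 0 g.

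This arithmetic is for weight. Length has the same loosely fixed starting point, but early weight loss does not apply to it.

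**4. Precision.** Let r be the baseline to follow-up correlation and L the baseline SD divided by the follow-up SD. In units of the follow-up variance:
- unadjusted change: 1 + L² − 2rL
- baseline-adjusted: 1 − r²

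With L = 1, the adjusted variance divided by the change-score variance is (1 − r²)/(2(1 − r)) = (1 + r)/2. This is 0.80 at r = 0.6, 0.85 at 0.7 and 0.90 at 0.8, so the saving is 20%, 15% and 10%.

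Equal SDs are doubtful because enrollment weight is confined to 1200 to 2500 g and later weight is not. Change-score variance divided by adjusted variance for other values:

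| L | r = 0.3 | r = 0.5 | r = 0.7 | r = 0.9 |
|---|---|---|---|---|
| 1 | 1.54 | 1.33 | 1.18 | 1.05 |
| 0.5 | 1.04 | 1.00 | 1.08 | 1.84 |
| 0.25 | 1.00 | 1.08 | 1.40 | 3.22 |

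The penalty runs from nil (when L = r) to more than threefold. If baseline size is already a covariate, modeling gain or attained size gives the same arm effect and standard error, so the penalty is nil.

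**5. What each covariate does.** Adjusting for enrollment weight alone does not remove a timing bias. It multiplies the shift by the slope of follow-up on baseline, r/L. With L = 1, the shifts in step 3 become 0.6 × 14.7 = 8.8 g to 0.8 × 58.7 = 46.9 g. Age at weighing is the term that addresses timing; baseline weight serves precision.

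**The case against.** This is a condensed article, and neither the full protocol nor an analysis plan is shown. The source of birth weight is operational detail and a covariate list is commonly left to the analysis plan. The regression allows further confounders, so baseline weight may well be among them. The 72-hour window and the birth-notification system are described without distinction by arm. Every gram and percentage above rests on assumed inputs, and a 24-hour difference in means would be a third of the whole window.

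Much of this stands, and it rules out three stronger readings that a reader might infer:
- **That the plan discards baseline adjustment.** Defining an outcome as gain does not exclude baseline as a covariate, and the text leaves the list open.
- **That growth results will be biased because intervention births are reached sooner.** Nothing in the document says so. Without an arm difference the effect is noise.
- **That an unblinded delivery team takes the baseline weight.** The article does not say who takes it. Training of Study Teams lists screening among the implementation team's training, while the Abstract has infants recruited by independent data collectors.

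What the objection does not answer is the definition itself. The article fixes birth as the starting point and describes a first contact up to three days later. That is a mismatch in what is stated, not a detail left out.

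**Conclusion.** The point holds for the starting point of the growth outcomes. As described, birth is not a time at which the trial measures many of its infants, and the gain will vary with age at first weighing if the screening weight is used in its place. That use is an inference from the screening and visit sections, strongest for home births.

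The certain consequence, given that use, is extra variability. Bias is conditional: about 15 to 59 g under the assumed loss and a 12 to 24 hour arm difference, and zero if timing is balanced. The precision gain from baseline adjustment is likewise conditional: 20 to 10% under equal variances and r of 0.6 to 0.8, nil if baseline is already a covariate, and outside that range for other variance ratios.

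This is a modest point on a secondary outcome and does not touch the mortality analysis. It is worth acting on because the correction uses the weight already needed for eligibility.

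**What to change.** 1. Define the baseline as the measurement at enrollment. If a facility birth weight is used for some infants, say for which and how the two sources are handled.
2. Analyze attained weight and length at each growth visit (or, equivalently, gain from enrollment) by linear regression on arm with enrollment weight or length as a covariate. Add age at enrollment weighing and exact age at follow-up where recorded, together with the cluster adjustment.
3. Report the distribution of age at first weighing by arm, so that readers can see whether timing was balanced. Gain from enrollment can still be shown descriptively.

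The cost is a few sentences and a small, dated wording change to a secondary outcome while the trial is running (data collection began in August 2019), best made before growth is compared by arm. The article does not say that hour of birth or of weighing is recorded, so age in hours may be missing for some infants. Age in days would then be a coarser substitute, and the rule for missing values should be stated.
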